## Abstract

**Background:**

Ketamine has recently attracted considerable attention for its rapid effects on patients with major depressive disorder, including treatment-resistant depression (TRD). Despite ketamine’s promising results in treating depression, a significant number of patients do not respond to the treatment, and predicting who will benefit remains a challenge. Although its antidepressant effects are known to be linked to its action as an antagonist of the N-methyl-D-aspartate (NMDA) receptor, the precise mechanisms that determine why some patients respond and others do not are still unclear.

**Objective:**

This study aims to understand the computational mechanisms underlying changes in the auditory mismatch negativity (MMN) response following treatment with intravenous ketamine. Moreover, we aim to link the computational mechanisms to their underlying neural causes and use the parameters of the neurocomputational model to make individual treatment predictions.

**Methods:**

This is a prospective study of 30 patients with TRD who are undergoing intravenous ketamine therapy. Prior to 3 out of 4 ketamine infusions, EEG will be recorded while patients complete the auditory MMN task. Depression, suicidality, and anxiety will be assessed throughout the study and a week after the last ketamine infusion. To translate the effects of ketamine on the MMN to computational mechanisms, we will model changes in the auditory MMN using the hierarchical Gaussian filter, a hierarchical Bayesian model. Furthermore, we will employ a conductance-based neural mass model of the electrophysiological data to link these computational mechanisms to their neural causes.

**Conclusion:**

The findings of this study may improve understanding of the mechanisms underlying response and resistance to ketamine treatment in patients with TRD. The parameters obtained from fitting computational models to EEG recordings may facilitate single-patient treatment predictions, which could provide clinically useful prognostic information.

**Trial registration:**

Clinicaltrials.gov NCT05464264. Registered June 24, 2022.

## Introduction

More than 264 million people globally have depression in the context of major depressive disorder (MDD), making it the leading cause of disability worldwide [1]. Despite their common use, approximately half of patients with MDD do not respond to their first antidepressant regimen [2–4], about a third continue to be unresponsive to two or more treatment trials (i.e., treatment-resistant depression [TRD]), and it takes 4–6 weeks to discern treatment response [2]. In recent years, ketamine has attracted considerable attention for its use in MDD, including in patients with TRD. While it has been used since the 1970s as a general anesthetic [5], it has more recently been found to exert rapid antidepressant effects in people with MDD, likely via its action as a *N*-methyl-D-aspartate receptor (NMDAR) antagonist [6]. It has been shown that a subanesthetic dose of IV ketamine alleviates depressive symptoms within as little as 40 minutes of a single infusion [7], with maximum efficacy typically occurring after 24 hours [8]. Indeed, response rates of over 60% have been observed after 24 hours in patients with TRD following a single infusion of ketamine [9]. Moreover, ketamine is highly effective in reducing suicidal ideation, with this effect being largely independent from its effects on mood [10]. Although ketamine has been known to cause short-term side effects such as agitation, psychotic-like symptoms, and cognitive impairment, these side effects rarely persist more than a few hours after administration [11].

While ketamine represents a potential breakthrough treatment for TRD, numerous aspects of its therapeutic effects are yet to be understood. While ketamine quickly alleviates depressive symptoms, these effects often require repeated infusions to be sustained [9, 12]. Furthermore, some patients with TRD do not improve despite receiving multiple infusions and it is currently not possible to predict who may benefit from this intervention in advance [13]. While changes in NMDAR-related plasticity are thought to contribute to the treatment response, the underlying neural mechanisms behind response compared to relapse are not yet elucidated [14]. Of note, the antidepressant effects of ketamine may be attributed to mechanisms other than NMDAR antagonism; multiple studies have demonstrated the roles of other receptors, such as the α-amino-3-hydroxy-5-methyl-4-isoxazolepropionic acid receptor (AMPAR), in producing antidepressant effects following ketamine treatment [15].

To address the above-mentioned challenges, we aim to elucidate the neural mechanisms of ketamine treatment by modeling ketamine-induced changes in auditory evoked potentials using the auditory mismatch negativity (MMN) paradigm. The MMN is a biological index of implicit learning, occurring when a sensory stimulus violates a statistical regularity in the environment [16]; for example, when a sequence of low tones is unexpectedly interrupted by a high tone. Formally, the MMN is defined as the difference waveform obtained when subtracting the electrophysiological response to a predictable (i.e., standard) stimulus from the response to an unpredictable (i.e., deviant) stimulus. It has long served as a marker of cognitive and functional decline in psychiatric disorders, whereby a smaller MMN amplitude corresponds with poorer levels of cognitive and psychosocial functioning [17]. Furthermore, since the MMN specifically reflects the flow of current through ion channels mediated by the NMDAR and is a relatively specific measure of postsynaptic potentials produced by the binding of glutamate to the NMDAR, it could potentially serve as a biomarker for determining whether a new treatment affects NMDAR responsiveness or to predict whether a specific patient might respond favorably to such a treatment [18].

Although the MMN response can vary in patients with MDD depending on different factors such as the type of auditory deviant or the stage of MDD or co-occurring conditions, it has been demonstrated that MMN amplitudes and/or latencies are significantly impaired in patients with MDD compared to healthy controls [19, 20]. The impaired MMN reflects reduced pre-attentive cognitive processes in MDD [21–24]. Ketamine’s effects on mood have been modeled using dynamic causal modeling (DCM) [25, 26] of event-related potentials (ERPs) under the MMN paradigm [27, 28]. It has been shown that ketamine increases the auditory MMN significantly in patients with MDD [27]. DCM also revealed that this increase was related to greater modulation of forward connectivity in response to a deviant tone, which was significantly correlated with antidepressant response to ketamine [28]. In addition to feedforward connectivity, mood improvements under ketamine have been attributed to increased synaptic gain. [6]. This may reflect increased α-amino-3-hydroxy-5-methyl-4-isoxazolepropionic acid receptor (AMPAR)-related synaptic plasticity following ketamine infusions [6]. However, the neural modeling approach used thus far (i.e., DCM for ERPs) does not explicitly model the contributions of distinct receptors, including AMPARs.

This study aims to understand the antidepressant and antisuicidal effects of ketamine using predictive processing theory, a paradigm in computational and cognitive neuroscience that has also attracted attention in psychology [29]. Predictive processing theory proposes that the brain forms top-down predictions to process sensory inputs and generates bottom-up PEs to improve these predictions; this process involves primarily NMDARs and AMPARs [30]. It is hypothesized that patients with MDD fail to adapt based on PEs due to rigid predictions [30]. Thus, we propose applying a hierarchical Bayesian model, the Hierarchical Gaussian Filter (HGF) [31, 32], to model trialwise changes in MMN. Using a conductance-based neural mass model, it is possible to link the computational mechanisms of the MMN response to the underlying neural causes, allowing for the study of the effects of NMDAR antagonism on the glutamatergic system [27, 28]. Our hypothesis makes connections to Bayesian theories of brain function [25, 33], which postulate that by blocking NMDARs and stimulating AMPAR signalling, ketamine impairs top-down predictions and enhances PEs. This interaction is believed to contribute to the rapid antidepressant effects of ketamine [30]. From these computational accounts, we propose that patients with TRD exhibit deficits in top-down (higher-level) belief precision restored under ketamine via NMDAR blockade and AMPAR upregulation. Moreover, we hypothesize that precision, AMPAR- and NMDAR-related parameters will define subgroups that predict different levels of therapeutic efficacy that are maintained with repeated ketamine infusions.

### Objectives

The objective of this study is to understand the computational mechanisms underlying changes in MMN following acute and repeated ketamine intervention. Subsequently, we aim to link the computational mechanisms to their underlying neural causes and use the neurocomputational model parameters to make individual treatment predictions.

## Methods

### Participants

This will be a single-centre study of 30 participants at St. Michael’s Hospital, Unity Health Toronto, where standard of care ketamine infusions are regularly performed in a monitored setting. Patients who are scheduled to receive ketamine treatment and are interested in participating in this study will be referred to the study coordinator. Approximately six patients are scheduled to receive IV ketamine every month. Participants aged 18 to 65 years who meet the Diagnostic and Statistical Manual for Mental Disorders (DSM-5) criteria for MDD are eligible for inclusion in the study. Participants must be in a major depressive episode at the time of screening, and have a total score of ≥10 on the Montgomery-Åsberg Depression Rating Scale (MADRS) [34]. Only those who are English-speaking and competent to consent, based on their ability to provide a spontaneous narrative description of the key elements of the study, will be included. Participants must have experienced a failure of at least two trials of antidepressant therapy during the current episode (i.e., TRD) and be receiving ketamine treatment clinically as administered by their clinician. Included participants will confirm that they are on stable doses of any concomitant psychotropic medications. If any changes to concomitant psychotropic medications are required per the patient’s standard of care, the participant will be withdrawn from the study. Patients with a history of bipolar disorder, psychosis, current diagnosis of substance use disorder or history of substance use disorder during the past year, excluding nicotine and caffeine use disorder, will be excluded from participating in this study.

### Trial design

This will be an observational study with a prospective design (Fig 1). According to the standard of care, patients will receive ketamine infusions twice a week for 2 weeks (4 total). Immediately prior to the first, second, and fourth infusions, patients will undergo an EEG scan with an auditory MMN task and simultaneous ECG recording. Clinical assessments of depression and anxiety symptoms as well as suicidal thoughts and behaviors will take place at baseline, after each ketamine infusion, and at follow-up, approximately one week after the last infusion.

**Fig 1 pone.0308413.g001:**
[figure not shown]
Study design.

### Screening and consent

Patients who are scheduled to receive ketamine treatment and have been consented to be contacted by the research team will receive a pre-screening telephone call. In a pre-screening telephone call, the study activities and timeline, as well as study goals will be explained to participants. A screening visit will be scheduled to take place over the phone. Before the screening process, the consent form will be reviewed over the phone and verbal consent will be obtained. If a participant meets the eligibility criteria for this study, they will be enrolled in the study. Participants will provide written informed consent during the first study visit.

### Sample size

We expect that at least 60% of TRD patients will respond to ketamine within the first 24 hours [35]. Furthermore, power analyses under the assumption of a medium-large effect size (i.e., Cohen’s *f* = 0.4) based on previous studies [32, 36, 37] and a 15% dropout rate indicate that N = 30 participants in total will be sufficient to test our hypotheses.

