### Data analysis

#### Clinical outcomes

Response will be defined as a reduction of 50% or more in the total scores of both the MADRS and GAD-7, and a 50% or greater reduction in item 10 of the MADRS scale, from baseline to the follow-up. Remission will be defined as a MADRS total score of 10 or below, assessed at the follow-up visit. C-SSRS and GAD-7 scores will be utilized to examine the association between biomedical signals and suicide and anxiety, respectively.

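### N = 30 is called sufficient for all hypotheses at f = 0.4; this holds for within-patient change but not for predicting response from one EEG per patient (about 47% power)

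*Protocol article*

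**What the plan says.** The Sample size section makes two statements. The first is an expectation that "at least 60% of TRD patients will respond to ketamine within the first 24 hours". The second, joined by a connecting word, reports that power analyses at Cohen's f = 0.4 and "a 15% dropout rate indicate that N = 30 participants in total will be sufficient to test our hypotheses", without singling any out.

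One hypothesis, at the end of the Introduction, is that precision, AMPAR-related and NMDAR-related parameters "will define subgroups that predict different levels of therapeutic efficacy". The Objectives add individual treatment predictions as an aim. The Introduction motivates this by noting that nobody can yet tell in advance who will benefit.

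EEG is recorded before infusions 1, 2 and 4, so each patient has three recordings, of which only the first precedes all treatment.

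The Clinical outcomes part of Data analysis states: "Response will be defined as a reduction of 50% or more in the total scores of both the MADRS and GAD-7". It also requires a 50% reduction in MADRS item 10, with all changes measured "from baseline to the follow-up". Trial design places this visit: "at follow-up, approximately one week after the last infusion".

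**The concern.** A single sufficiency statement covers two kinds of question. Change within a patient across three recordings benefits from repeated measurement, and each patient serves as his or her own control. Whether a parameter separates those who will respond from those who will not is a comparison between patients. If it is to be prognostic, it rests on one pre-treatment recording each. The same f and the same N do not buy the same power for both.

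If the sentence stands, a null prediction result could be taken as adequately powered evidence against the biomarker, although the study had about even odds of missing an effect of the assumed size. A significant result from a comparison with such low power would tend to overstate the effect.

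The response rate raises a separate question. The rate describes early response, whereas the study's responder groups are formed later and by a stricter composite rule.

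**Working it through.** **Inputs from the protocol article.** N = 30, f = 0.4 and 15% dropout (Sample size); response of at least 60% (same section, 24-hour rate); three EEG visits (Trial design; Neurocomputational mechanisms and model).

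**Assumptions, not in the article.** Two-sided alpha 0.05; 80% power as benchmark; within-patient correlation ρ from 0 to 0.7; for two equal groups d = 2f = 0.8.

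**Completers.** 30 × 0.85 = 25.5, taken as 25. In reverse, 25 / 0.85 = 29.4, which rounds up to 30. At 60%, 25 completers split into 15 responders and 10 non-responders.

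**The plan's own figure.** The article does not tie N = 30 to one test, so it cannot be reproduced uniquely. It is compatible with a within-patient design: two visits, 80% power and ρ = 0.1 need 25 completers, hence 30 enrolled. Three visits at 80% power need 22, 16 or 12 completers at ρ = 0, 0.3 or 0.5, hence 26, 19 or 15 enrolled.

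**Within-patient change, 3 visits, 25 completers.** Noncentral F with λ = N·m·f²/(1 − ρ) and df 2 and 48. At ρ = 0, λ = 25 × 3 × 0.16 = 12 and power is 86%. At ρ = 0.5, λ = 24 and power is 99%. At ρ = 0.7, λ = 40 and power is over 99%.

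**Responders versus non-responders, one measurement per patient.** Noncentral t with δ = d·√(n₁n₂/(n₁+n₂)). For 15 vs 10, δ = 0.8 × √(150/25) = 1.96 on 23 df, against a critical value of 2.07.

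| Split | Power at d = 0.8 |
|---|---|
| 15 vs 10 | 46.7% |
| 13 vs 12 | 48.2% |
| 9 vs 16 | 45.2% |
| 18 vs 7 | 40.6% |
| 18 vs 12 (no dropout) | 54.5% |

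Holding f = 0.4 exactly with 25 completers gives 48.3%. The effect detectable with 80% power at 15 vs 10 is d = 1.19. For 80% power at d = 0.8 one needs 52 completers in equal groups or 54 at a 60/40 split. After dropout this is 52 / 0.85 = 61.2, so 62 enrolled, or 54 / 0.85 = 63.5, so 64. A regression on one predictor with f² = 0.16 also needs 52 completers, so dichotomising response is not the cause.

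**Other between-patient readings, 25 completers, equal groups.**

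- Contrast averaged over three visits, λ = N·m·f²/(1 + (m − 1)ρ), df 1 and 23. At ρ = 0.3, 0.5 and 0.7, λ = 7.5, 6 and 5, and power is 75%, 65% and 57%. At ρ = 0 it is 91%.
- Group-by-visit interaction at f = 0.4, λ = N·m·f²/(1 − ρ), df 2 and 46: 86% at ρ = 0, over 99% at ρ = 0.7.

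**Response rate, side by side.** The Sample size section gives at least 60% within 24 hours. Clinical outcomes requires three 50% reductions together (MADRS total, GAD-7 total, MADRS item 10) at a visit about one week after the fourth infusion. Neither the time point nor the definition agrees, and the section offers no rate for the latter.

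**The case against.** The strongest reply is that the article does not fix the 47%. The Sample size section ties N = 30 to no particular test, and the design yields three recordings per patient. The subgroup hypothesis also speaks of levels of efficacy maintained over repeated infusions, which a group-by-visit interaction could address with 86% power or more. This stands. A reader might infer from the 47% that the study is underpowered as a whole, or for every comparison of responders with non-responders. The documents do not support either inference. What remains is that the interaction and the visit-averaged contrast use recordings made after treatment has begun, so neither is prediction in advance.

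A reader might also infer that N = 30 is miscalculated. It is not shown to be: it is compatible with within-patient designs and adequate for them.

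Nor does the article show that the 60% entered the power analysis. It stands in its own sentence, and responder fractions from 30% to 70% move the single-visit power only between 41% and 48%. The mismatch therefore concerns what the section tells the reader about the responder groups. It does not explain the shortfall.

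Finally, prediction is worded cautiously in the Conclusion and Discussion and comes second in the Objectives. That softens the aim, but it does not limit the sufficiency sentence.

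**Conclusion.** The point holds in a limited form and should be fixed. The unqualified sufficiency statement is right for within-patient change across Visits 1, 2 and 4 (86% to over 99% power with 25 completers). It is not right for the prediction hypothesis read as pre-treatment prediction from one measurement per patient. There, power is about 47% at 15 vs 10, 45% to 48% for splits from 9 vs 16 to 13 vs 12, and 55% if nobody drops out. These figures depend on two-sided alpha 0.05, d = 0.8 and a single measurement, which are assumptions of this check. No reasonable split of 25 completers rescues the single-visit comparison.

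The response-rate mismatch is independent of any power assumption: the only rate given belongs to another time point and another definition.

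**What to change.** Keep N = 30 and reword the Sample size paragraph in three places:

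- Limit the sufficiency claim to within-patient change in the MMN and model parameters across Visits 1, 2 and 4.
- Label prediction of response from baseline or any single visit as exploratory. Give either its conditional power (about 47% at d = 0.8 with 15 vs 10 completers, two-sided 0.05) or the effect detectable at 80% power (d about 1.2).
- Replace the 24-hour rate, or add to it, an assumed rate for response as Clinical outcomes defines it at the follow-up visit.

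The cost is one paragraph of text and no extra patients or visits. The price is a less favourable statement of adequacy for the prediction aim. Sizing that aim at d = 0.8 instead would take 62 to 64 enrolled patients, about twice the planned number.

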### Retention strategy

Participants will be compensated CAD $20 per in-person EEG visit, for a total of CAD $60. The research staff will give each participant a reminder call before each recording session. Participants will no longer be eligible to continue the study if they miss more than one infusion.

### Data collection

#### Clinical outcomes

This study will evaluate depressive symptoms, anxiety symptoms, and suicidal risk at baseline, after each ketamine infusion, and at the one-week follow-up visit. These assessments will be conducted using the MADRS, Columbia Suicide Severity Rating Scale (C-SSRS), and Generalized Anxiety Disorder 7-item (GAD-7). The MADRS [34] is a 10-item clinician-rated scale designed to measure MDD severity and detect changes due to treatment. Suicide risk will be examined using MADRS item 10 and the C-SSRS [38], a semi-structured clinical interview, which utilizes a set of prompts and questions to obtain more complete information on events suggestive of suicidality. Additionally, the GAD-7 [39] is a 7-item self-rated questionnaire designed for assessing generalized anxiety disorder.

#### EEG and ECG

EEG and ECG data will be collected immediately before the first, second, and fourth treatment visits. A Biosemi ActiveTwo system will be used to collect EEG data at a sampling rate of 512 Hz during the auditory MMN task. A 32-electrode configuration based on the extended 10–20 system, an internationally recognized method for electrode placement, will be utilized. To accurately identify and correct eye movement artifacts, the horizontal and vertical electro-oculogram (EOG) measures will be recorded through electrodes placed lateral to each eye, as well as electrodes placed below each eye. Reference electrodes will be placed bilaterally on the mastoids. The scalp electrodes will be affixed using a cap, and a water-based conductive gel will be applied to ensure optimal conductivity and signal clarity. The ECG signal will be recorded with an additional electrode, part of the EEG system, attached on the participant’s wrist. This setup is designed to obtain a high-quality data acquisition without potential physiological interference.

#### MMN task

The auditory MMN paradigm has been previously used in MDD patients following ketamine interventions [40, 41], and was shown to be safe and have no impact on symptoms. EEG data will be collected during an MMN paradigm specifically designed to minimize the correlation between low-level and high-level precision-weighted prediction errors (for details, see Weber et al. [42]).

This auditory MMN task consists of a train of alternating tones of different frequencies (528 Hz versus 440 Hz) presented for 70 ms including 5 ms fade-in and 5 ms fade-out (Fig 2). To investigate individual differences in the expression of hierarchical precision-weighted prediction errors (PEs), we will systematically vary the probability of the tones. The task consists of two types of phases: stable phases were defined as periods where the probability of hearing the same tone remained constant for at least 90 trials and volatile phases were all other phases (see volatility structure in Fig 2A). Auditory stimuli will be presented using PsychToolbox (PTB3, psychotoolbox.org) and participants will be directed to look at a fixation point for the duration of the experiment, which lasts a total of 20 minutes.

